### Primary outcome

#### Pain

The VAS is an extensively used psychometric response scale that assesses participants’ pain severity. It requires participants to rate their pain severity along a horizontal line with ten points, with 0 and an image of a smiling face indicate no pain, and 10 and an image of pain and discomfort indicate severe pain. The VAS has demonstrated excellent reliability and validity, with a high internal consistency of ICC = 0.91 [23]. The minimal clinically important difference (MCID) for people with CLBP is 1.5 cm, as reported in a previous study [56].

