### Secondary outcomes measurements

#### Disability

The Persian version of the Oswestry questionnaire will be used to examine the degree of disability in participants with CLBP [57]. This questionnaire consists of 10 six-option items that assess an individual’s capacity to perform daily activities. Each item assigns a disability score to the activity, ranging from zero (no pain during the desired function) to five (severe pain prevents performance). The Oswestry Disability Index is the sum of the scores of these ten items, multiplied by two, producing a value between 0 and 100. A zero score indicates that a person can perform daily activities without pain. Scores between 1 and 20 indicate mild or minor disability, 21 to 40 indicate moderate disability, 41 to 60 indicate severe disability, and 61 to 80 indicate a debilitating disability. Scores of 81 and higher indicate that a person is bed-bound or exaggerating symptoms. The validity of the Oswestry questionnaire has been confirmed with a Cronbach’s alpha of 75%, and its reliability has been reported with a correlation coefficient of 0.92 [58]. The lowest MCID in individuals with CLBP is 10 points [59].

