#### Fear-avoidance beliefs

The Persian version of the Fear-Avoidance Beliefs Questionnaire (FABQ) [60] will be used to assess patients’ fear-avoidance beliefs during physical activity and work. It consists of 16 items related to physical activity (FABQ-PA) and work (FABQ-W) that affect patients with LBP. For FABQ-W, those scoring 34 or higher out of a possible 42 points are less likely to return to work within four weeks. In contrast, a score of 15 out of 24 points on the FABQ-PA indicates fear-avoidance beliefs regarding the physical activities [60]. The Persian version of the FABQ has demonstrated validity and reliability (ICC = 0.80) for measuring fear-avoidance beliefs in patients with CLBP [60]. A variation of 4 points for FABQ-PA and 7 points for FABQ-W represents the MCID in CLBP [61].

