#### Fear of movement

The Tampa Scale of Kinesiophobia (TSK) measures fear of movement or kinesiophobia in patients with LBP [64]. The total score on this scale ranges from 17 to 68, with 68 indicating severe fear of movement, 37 indicating fear of movement, and 17 indicating no fear. It has been translated and validated into Persian, showing good reliability (ICC test-retest = 0.86) [65]. The MCID for individuals with chronic musculoskeletal pain is 4.5 points [66].

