### Statistical analysis

The sample size has been estimated for the primary outcome of pain intensity (VAS), with emphasis on the proportion (%) of patients with improved CLBP on the VAS. The minimal important change in VAS is reported to be 15 mm [70]. Accordingly, we expect a minimal difference of 20% between the intervention groups in the proportion of patients with an improved VAS score (at least 15 mm) [27]. To detect a difference in main effects (i.e., PNE plus NMS vs NMS), the sample size calculation using G*Power software and like previous studies in the field of PNE (30), with an effect size difference of 0.25, an alpha value of 0.05 (two-sided test), and power (1 × b) 0.80, results in a required total sample size of 60 participants (30 patients per group). Assuming a dropout rate of 20%, we will enroll 30 patients per group.

A 2 × 2 variance analysis (treatment group × time) will be conducted using a mixed-model analysis design. The percentage change will be calculated for each variable compared to the baseline. The effect size (ES) using partial eta squared (ηp2) will be calculated to measure the clinical meaningfulness [71]. For ITT analyses, group means will replace missing data during the post-test. There will be no additional analyses (e.g., subgroup and adjusted analyses). All data analyses will be conducted using the SPSS software version 26 (IBM Corp., Armonk, NY, USA) at an alpha level of 0.05.

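### Partial eta squared is named as the measure of clinical meaningfulness, but it cannot show whether a group difference reaches the MCIDs that the protocol quotes in scale points

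*Protocol article*

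**What the plan says.** The Statistical analysis section sets the model: "A 2 × 2 variance analysis (treatment group × time) will be conducted using a mixed-model analysis design". It then adds two summaries: "The percentage change will be calculated for each variable compared to the baseline", and "The effect size (ES) using partial eta squared (ηp2) will be calculated to measure the clinical meaningfulness". It closes off further work with "There will be no additional analyses (e.g., subgroup and adjusted analyses". It names no between-group difference in scale points.

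The outcome sections give a yardstick in absolute units for each instrument:

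- Pain (VAS): "The minimal clinically important difference (MCID) for people with CLBP is 1.5 cm".
- Disability (ODI): "The lowest MCID in individuals with CLBP is 10 points".
- Fear-avoidance beliefs: "A variation of 4 points for FABQ-PA and 7 points for FABQ-W represents the MCID in CLBP".
- Self-efficacy (PSEQ): 9 points.
- Fear of movement (TSK): 4.5 points.

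In the Statistical analysis section only the VAS threshold reappears, as 15 mm. It is used in the sample-size rationale, where it defines an improved patient. No analysis of that proportion is named afterwards.

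**The concern.** Whether a difference matters to patients is a question about its size on the scale that patients scored. Partial eta squared answers another question: what fraction of the variance, after other model terms are set aside, goes with one term. It carries no sign, so it does not say which arm did better. The same difference in points yields a larger or smaller value according to how alike the patients are and how strongly their post-test scores follow their baseline scores.

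The article therefore gives the job of judging clinical meaning to a statistic that cannot be set beside its own MCIDs. A report that follows this text could call a result clinically meaningful, or not, without stating whether pain fell by 1.5 cm more in one arm than in the other.

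**Working it through.** **Inputs from the protocol article.** 30 patients per arm (Randomization; Statistical analysis), a 2 × 2 group-by-time model (Statistical analysis), and the MCIDs listed above.

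**Assumptions.** The article gives no SD and no pre-post correlation ρ. I take VAS SDs of 1.0 to 2.5 cm, equal at both times and in both arms, and ρ from 0.3 to 0.7. I take the treatment comparison to be the group-by-time term. No published partial eta squared is at hand to reproduce.

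**Formula.** With two groups and two times, the group-by-time F equals t² from comparing change scores. For a between-group difference in change δ:

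- SE = SD × √(2(1−ρ)) × √(2/30)
- t² = δ²/SE² = 7.5 × (δ/SD)² / (1−ρ)
- partial eta squared = t² / (t² + 58)

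**Step 1: a VAS difference exactly at the MCID (δ = 1.5 cm).**

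- SD 1.0, ρ 0.7: t² = 7.5 × 2.25/0.3 = 56.25, so 56.25/114.25 = 0.49.
- SD 2.5, ρ 0.3: t² = 7.5 × 0.36/0.7 = 3.86, so 3.86/61.86 = 0.06.

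| SD (cm) | ρ = 0.3 | ρ = 0.5 | ρ = 0.7 |
|---|---|---|---|
| 1.0 | 0.294 | 0.368 | 0.492 |
| 1.5 | 0.156 | 0.205 | 0.301 |
| 2.0 | 0.094 | 0.127 | 0.195 |
| 2.5 | 0.062 | 0.085 | 0.134 |

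**Step 2: a VAS difference below the MCID (δ = 1.0 cm, ρ = 0.5).** At SD 1.0, t² = 7.5 × 1/0.5 = 15.0, so 15.0/73.0 = 0.205. At SD 2.5, t² = 7.5 × 0.16/0.5 = 2.4, so 2.4/60.4 = 0.040. The first exceeds the 0.085 that a full 1.5 cm gives at SD 2.5 and the same ρ. A larger partial eta squared therefore need not mean a larger difference in points.

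**Step 3: the reverse reading.** Solving for δ gives δ = SD × √(58e/(1−e) × (1−ρ)/7.5), where e is partial eta squared. Two illustrative values of e, over the same assumed range:

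- e = 0.06 corresponds to 0.38 to 1.47 cm.
- e = 0.14 corresponds to 0.61 to 2.35 cm, which spans both sides of 1.5 cm.

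**Step 4: the other instruments, each at its own MCID, ρ 0.3 to 0.7.**

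| Instrument | MCID | Assumed SD | Partial eta squared |
|---|---|---|---|
| ODI | 10 | 10–20 | 0.04–0.30 |
| FABQ-PA | 4 | 4–8 | 0.04–0.30 |
| FABQ-W | 7 | 7–13 | 0.05–0.30 |
| PSEQ | 9 | 9–15 | 0.06–0.30 |
| TSK | 4.5 | 5–10 | 0.04–0.26 |

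Within these ranges, no fixed value marks the MCID for any instrument.

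**Side check: percentage change.** A fall of 1.5 cm is 1.5/5 = 30% at the entry minimum of 5 on VAS (Inclusion criteria) and 1.5/10 = 15% at the top of the scale. For TSK, "The total score on this scale ranges from 17 to 68", so the origin is arbitrary: 4.5 points from 37 is 4.5/37 = 12.2% of the raw score but 4.5/(37−17) = 22.5% of the score above its minimum.

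**The case against.** The strongest reply is that the article sets no cut-off for partial eta squared and ties no decision to it, so no rule exists that could fail. That stands in part. A reader might infer that the plan will produce wrong conclusions about benefit. The text does not support that: the hypothesis test and alpha are untouched, and what is shown is that interpretation can be misled. The sentence still assigns clinical meaningfulness to this statistic, so it is a choice the article makes, not a detail left to an unseen analysis plan.

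A second reply is that partial eta squared can be converted to points. That is true once the SD and correlation are known, but the article states no such step.

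A third is that MCIDs are not absent from the Statistical analysis section, because the 15 mm threshold is there. It is, but only in the sample-size rationale. That text applies it to individual patients, so setting a mean difference between arms against the same figure is a further step that should be acknowledged.

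Two other strong readings also fail:

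- **Every outcome has an MCID.** This holds for the instruments described. Exercise anxiety, listed as a secondary outcome in the Abstract, has neither an instrument nor an MCID.
- **Percentage change is unusable because a baseline may be zero.** VAS cannot be zero at entry, where at least 5 is required. A zero on another scale is possible in principle, but the article does not say whether the percentage is taken per patient or on group means. It attaches no test or threshold to it, so it is a descriptive summary, and its dependence on baseline and on the TSK origin is a side note.

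**Conclusion.** The concern holds in a limited form. The Statistical analysis section names a measure of clinical meaningfulness that cannot be read against the protocol's own absolute MCIDs. For a VAS difference of exactly 1.5 cm it can lie anywhere from about 0.06 to 0.49. That width rests on the assumed SDs and correlations, and narrower assumptions would narrow it. The dependence itself follows from the formula and needs no assumed figure. The consequence is for interpretation only, so this should be corrected but does not threaten the validity of the test.

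**What to change.** Replace the sentence on clinical meaningfulness with text to this effect: for each outcome, clinical meaning will be judged by the between-group difference in change from baseline, in scale points with a 95% confidence interval, read against the MCID quoted for that instrument; for VAS, the proportion of patients improving by at least 15 mm will also be reported by arm; partial eta squared will be given as a descriptive statistic only.

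The responder proportion belongs there because the sample-size text uses 15 mm as a threshold for individual patients. The amendment should also say that reading a group difference against an MCID is an interpretive aid.

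The interval also shows precision in the units that matter. Under the assumptions above, SE for VAS runs from 0.20 cm (SD 1.0, ρ 0.7) to 0.76 cm (SD 2.5, ρ 0.3). With a t quantile of 2.00 on 58 degrees of freedom, the half-width is about 0.40 to 1.53 cm.

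An unadjusted difference in change is enough to cure the defect. If a baseline-adjusted difference is preferred, the sentence ruling out additional and adjusted analyses must be amended to allow it. In either case that sentence should not be left to exclude the responder proportion. Where percentage change is kept, show absolute change beside it.

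The cost is a small amendment to the analysis text and no new data. Trial status says recruitment began in March 2024 and was expected to end by February 2025, so the amendment should be dated and fixed before analysis.

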### Randomization

The principal investigator ([name]) will generate the allocation sequence using an online random number generator (Random.org). Patients will be randomly assigned to one of two groups in a ratio of 1:1 as follows: Group 1 Experimental-PNE plus NMS (n = 30) or Group 2 Control–NMS (n = 30). Randomization will draw numbers from 1 to 60, prepared in advance and placed in sealed opaque envelopes in a box (Fig 1). Participants will be told which intervention they were randomized to at the end of the study [44–46].

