#### Adherence

The analysis will follow intention-to-treat (ITT) principles, including all patients based on randomization, regardless of whether they have received the primary interventions [37]. The principal investigator will document adherence to the exercise regimen in a weekly report. Moreover, missing data will be reviewed, and sensitivity analyses will be conducted when necessary. During the implementation period of the main intervention, weekly reminder calls and text messages will be sent to participants to remind them of the meetings [67,68].

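### Filling missing post-test scores with the group mean understates the standard error: at the plan's own 20% dropout, the planned group × time test has a false-positive rate of about 7–8%, not 5%

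*Protocol article*

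**What the plan says.** The protocol article's Adherence section sets the analysis population: "The analysis will follow intention-to-treat (ITT) principles, including all patients based on randomization". It adds that missing data will be looked at and that sensitivity analyses will follow if needed, without saying which or under what condition.

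The Statistical analysis section gives the method for missing values: "For ITT analyses, group means will replace missing data during the post-test". It names one inferential analysis: "A 2 × 2 variance analysis (treatment group × time) will be conducted using a mixed-model analysis design". Testing is "at an alpha level of 0.05", matching the two-sided 0.05 in the sample-size text. On losses it says: "Assuming a dropout rate of 20%, we will enroll 30 patients per group". It uses partial eta squared as the measure of clinical meaningfulness and rules out additional analyses, giving subgroup and adjusted analyses as examples. No variance correction and no multiple imputation is mentioned.

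The section on concomitant care, modifications and adverse effects says that patients in the intervention group who have side effects or worsen severely leave the study.

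**The concern.** A filled-in post-test score equals the mean of the scores observed in that arm. It carries no information about the missing patient and no post-test variation, yet the analysis counts it as one more independent observation. The sample size and degrees of freedom are overstated, and the standard error of the comparison is too small. This happens even when patients are lost purely at random, and it affects the primary outcome and every secondary outcome.

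A second problem is bias. Using the arm's observed mean supposes that those who left would have scored like those who stayed. If patients leave because they are doing badly, the arm's mean looks better than it was, by the fraction missing times the gap between dropouts and completers.

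**Working it through.** **Inputs from the protocol article.** n = 30 per arm (Randomization; Statistical analysis); 20% dropout, so m = 24 observed and 6 filled per arm; alpha 0.05 two-sided; a 2 × 2 group × time analysis. The interaction test in that design equals a t-test on change scores.

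**Assumptions not in the document.** Values are missing completely at random and equally in both arms; the group mean is the patient's own arm mean; the post-test is the 8-week visit; baseline and post-test have equal variance (set to 1) and correlation r between 0 and 0.9.

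**Step 1: without the rule.** Simulating null trials (100,000 per setting) and testing only the observed changes gives a false-positive rate of 4.9–5.1%, which reproduces the plan's 5%.

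**Step 2: the planned interaction test with the rule.** Write k = (m − 1)/(n − 1) = 23/29 = 0.793. Dropouts keep their real baseline, so for one arm's mean change:

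- actual variance = 1/m + 1/n − 2r/n
- variance the analysis reports, on average = (1 + k − 2rk)/n
- false-positive rate ≈ 2[1 − Φ(1.96 × SE ratio)], with SE ratio = √(reported/actual)

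| r | actual | reported | SE ratio | approximate rate |
|---|---|---|---|---|
| 0 | 0.0750 | 0.0598 | 0.893 | 8.0% |
| 0.5 | 0.0417 | 0.0333 | 0.894 | 8.0% |
| 0.9 | 0.0150 | 0.0122 | 0.901 | 7.7% |

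For r = 0.5: actual = 1/24 + 1/30 − 1/30 = 0.0417; reported = (1 + 0.793 − 0.793)/30 = 0.0333; √0.80 = 0.894; 2[1 − Φ(1.753)] = 0.080.

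Simulation (100,000 null trials per setting) gives 7.3–8.1% across r = 0 to 0.9, with the lowest value at r = 0.9.

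**Step 3: other dropout rates, same test, simulated.** About 6% at 10% missing (5.9–6.3%) and 9–10% at 30% missing (9.2–10.1%).

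**Step 4: other tests at 20% missing.** The group main effect in the same 2 × 2 analysis runs at 7.8–8.2%. A comparison of post-test scores alone has SE ratio √((24/30) × (23/29)) = 0.797 and a rate of P(|t46| > 2.002 × 0.797) = 11.8%, with 11.7–12.1% simulated. ANCOVA on the post-test gives 11.7–12.8%.

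**Step 5: partial eta squared.** It is built from the same error sum of squares, in which post-test variance is cut to 23/29 = 0.79 of its value. For the group main effect at r = 0.5 the error variance is (1 + 0.793 + 0.793)/3 = 0.86 of what complete data would give. For the interaction the covariance with baseline is cut too, so the ratio (1 + k − 2rk)/(2 − 2r) is 1.317/1.4 = 0.94 at r = 0.3, 1.00 at r = 0.5 and 0.683/0.6 = 1.14 at r = 0.7. The effect size is therefore distorted, in a direction that for the interaction depends on r. The false-positive rate is raised at every r examined.

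**The case against.** The strongest objection concerns size. A reader might infer a false-positive rate as high as 12%, or a standard error only 0.80 of its proper value. Those figures belong to a post-test-only comparison or ANCOVA. The plan names neither, and it rules out adjusted analyses. In the planned group × time test the dropouts' real baselines keep some variation in the filled change scores, so the inflation is about 2 to 3 percentage points and the standard error is about 0.89 of its proper value. This objection stands, and the point is limited accordingly.

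The 20% is also only a planning figure. The article plans weekly calls and texts, catch-up for missed sessions and flexible assessment times. If losses stay near 10%, the rate is about 6%. That too stands, but the rule should work at the dropout the plan itself assumes.

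The Adherence section allows sensitivity analyses. They are conditional and unspecified, and they leave the stated intention-to-treat analysis as it is. The words mixed-model design do not help either, because a model fitted after filling treats the filled values as observed.

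Finally, a reader might infer that the rule favours the combined arm. The document does not support that. The rule on leaving the study makes it doubtful that dropouts resemble completers, but which arm gains, and by how much, depends on unknown differences in dropout. With similar losses and similar reasons in both arms, the bias could be small.

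**Conclusion.** The concern holds in a limited form. The article commits to a method that cannot deliver its own 5% level: about 7–8% for the planned interaction and about 8% for the group main effect at 20% dropout. These figures rest on equal, completely random dropout, own-arm means and r between 0 and 0.9, and they cover only the understated standard error. Bias from informative dropout is a separate, unquantified concern. Because the article states the rule outright, a separate analysis plan that is silent on it would not remove the problem. Correction is needed before the data are analysed.

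**What to change.** Delete the group-mean sentence. State instead that all randomised patients are analysed with a likelihood-based mixed model (for example the SPSS MIXED procedure) on the observed baseline and 8-week values, without single imputation, and that the test is the group × time contrast at 8 weeks. Patients without a post-test still contribute their baseline. If the 6-month visit enters the model, say which contrast is primary.

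Other choices would also restore the 5% level under random dropout, as the observed-change analysis in Step 1 shows. The mixed model is preferable because it keeps every randomised patient with any data. Multiple imputation with a shift for dropouts would be a suitable sensitivity analysis for informative dropout, but it is optional.

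The cost is protocol wording, plus slightly larger standard errors and p-values. No extra patients or data are needed. The change should be dated and made before unblinded analysis.

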### Plans to give access to the full protocol, participant-level data and statistical code

All the data required to support the protocol will be supplied upon request. All datasets and statistical code requests will be submitted to the corresponding author for consideration. Access to anonymized data may be granted following a consensus involving the trial statistician and Priment Clinical Trials Unit team. No images or other personal or clinical information about the participants are included in this report or will be included in future reports of the trial results. The participants’ information materials and informed consent forms will be obtained from the corresponding author upon request.

### Patient involvement

Patients will be involved in the study planning so that the time for the call (report pain and update exercise), time of the start of the first session of exercise, time to assessment (at baseline, after 8 weeks, and 6 months), (PNE plus NMS and NMS groups) can be adapted according to their preferences, availability, and comfort. We will encourage patients to self-report their feelings about the volume, intensity, or type of exercise, and inform their physiotherapist accordingly.

### Post-trial care and dissemination policy

The interventions involved in this trial are expected to cause minimal harm. There is no anticipated harm or compensation for trial participation. The results obtained will be disseminated at the national and international levels in the form of scientific articles published in relevant peer-reviewed journals.

## Discussion

In this paper, we present a protocol for an RCT that aims to investigate the effects of PNE plus NMS compared with NMS alone on pain, functional and psychological outcomes in 60 patients with CLBP. The synergy between PNE and NMS may provide comprehensive benefits by simultaneously reducing pain, improving functional capacity, and alleviating psychological distress, thus shedding light on the recovery process in patients with CLBP [22,32].

As a strength, this protocol offers a fresh perspective on the management of CLBP. First, combining PNE with NMS addresses both the physical and psychological impairments of CLBP. The combined approach is expected to improve patient outcomes more effectively than either intervention alone, thereby enriching the therapeutic options for CLBP. Second, the protocol design follows international reporting guidelines (SPIRIT, CONSORT, TIDIER) [33–35,72] and adopts single-blind assessments and ITT analysis to ensure rigorous and high-quality data collection and interpretation. Third, the study considers diverse outcome measures (e.g., pain intensity, functional disability, and psychological factors) in accordance with the biopsychosocial model in CLBP [14]. Taken together, these actions represent useful strategies for overcoming the methodological issues presented in RCTs on NMS [27–29], thereby contributing to the advancement of knowledge on this topic.

However, there are several limitations to this study. The sample size, although statistically adequate, may limit the generalizability of the results to the broader CLBP population. Further studies with larger sample sizes are required to confirm our future findings. Another limitation is the monocentric design, as the study will be conducted within a single outpatient healthcare setting and will consider patients with CLBP (not recurrent LBP) [30] exclusively from Iran, impacting the external validity of the findings. Additionally, the lack of a validated Persian version of the Central Sensitization Inventory [22,32] will hinder exploration of the relationship between pain improvement and central sensitization. Furthermore, we have considered patient-reported outcomes (PROs) as primary and secondary outcomes. Although PROs are commonly used in RCTs, they are prone to limitations, such as response bias, recall bias, and the subjective nature of self-reported data [73]. Finally, excluding individuals above the age of 60 and below 30 years old from the study will restrict the applicability of our findings to these specific age groups. Further research should incorporate a wider range of age groups and investigate long-term outcomes to better understand the effectiveness of the interventions.

In conclusion, our RCT can contribute to advancing the management of CLBP and optimizing patient care, thus providing new insights to the rehabilitation field.

